### Secondary (exploratory) aims

#### Reference scores

We plan to develop a set of preliminary reference scores to facilitate comparison of DAZ scores across countries. From the full validation study sample, a subsample of children who have not experienced prior exposure to major known biological and environmental risk factors is selected (ie, ‘reference subsample’) (table 3). Such an approach relies on the assumption that the attainment of basic developmental milestones captured by the GSED of children who are free of major risk factors is relatively similar globally.^23^

**Table 3 T3:** ‘Reference’ subsample exclusion criteria (healthy subsample)

Sample	Exclusion criteria
Minimum subsample of ‘reference’ children per site n=522	Below secondary maternal education (<6 years of schooling) Birth weight <2500 g Gestational age <37 completed weeks (259 days) and ≥42 completed weeks (294 days) (assessed by ultrasound) Undernutrition (weight for age, length for age, OR weight for height Z score of <–2 on the WHO Child Growth Standards) at the time of developmental assessment Known severe congenital birth defect History of birth asphyxia OR neonatal sepsis requiring hospitalisation Known neurodevelopmental disorder/disability (Severe visual problems, seizures, hearing impairment) OR other chronic health problems (ie, congenital heart disease)

To develop the reference scores, we will fit GAMLSS^24^ to flexibly model both conditional means, conditional SD of scores, and, if necessary, conditional skewness and kurtosis. We will test our assumption that the distribution of scores is equivalent across sites by adding a site indicator at each moment of the distribution, and testing site effects for their statistical significance. Where possible, we will conduct standardisation of scores to assist with the interpretation of scores by pooling data across countries. We will report the corresponding parameters of the GAMLSS model at appropriate ages.

#### Adaptive testing

We will determine whether adaptive testing is a feasible and valid option to measure child development within the GSED (box 2). Adaptive testing^25^ is an administration method that continually adapts to the level of the child’s performance, thereby reducing test administration time. Previous simulations^26^ indicated that theoretically substantial gains in the precision of scores are possible when using adaptive testing even if administering fewer items.

Box 2Adaptive testing validation methodologyWe investigate the feasibility by applying adaptive testing in addition to the traditional ‘fixed’ GSED administration methods in the subsample designated for predictive validity analyses (n=502 per site) in three sites. The adaptive test is executed using tablets that are specially programmed to continually adjust child’s score after each item is administered, and to suggest the next item based on the answers already received (eg, a more difficult item for a child with a higher score, an easier item for a child with a lower score). Once the programme establishes a reliable score, the administration is terminated. Both the adaptive test and the fixed test are administered with the same subsample during two separate visits alternating the order of administration to investigate the difference between the two modes of administration. We will investigate the following: the variance of user experience as a function of the average difficulty of milestones (leniency); the comparison of the D-score distribution under the adaptive testing procedure with the D-score distribution under the fixed GSED administration (using a z-test to assess the equivalence of the two modalities and plotting the results to show the level of concordance) and relation of the difference between the two D-scores to background variables.

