#### Sampling frame and schemes

Sample size for recruitment within each site is 1248 children (total 8736 children) across seven countries. After consent is provided, children are allocated by sex and age groups using a randomization procedure to one of several sampling schema (eg, predictive, reference-score, reliability; figure 2). See sampling in online supplemental table S1 for sampling frame. Out of the full site sample of 1248 children, 504 children per site are randomly selected for re-evaluation 6 months later to assess predictive validity (primary aim). A second scheme indicates the minimum subsample of children needed to calculate preliminary reference scores (secondary aim) that will facilitate cross-country comparisons. To maximise precision of parameter estimates, larger quotas are kept for the youngest age brackets where rates of development are accelerated. A third scheme addresses inter-rater reliability for 90 children per site using two assessors who independently assess the same child sequentially or within 24 hours^12^ (We note that this procedure differs from typical inter-rater reliability (IRR) designs which involve simultaneous scoring of a single assessment. This sequential design was necessitated by logistical constraints. Given that this design captures both variance due to differences in raters and differences in occasions, the observed IRR represents a lower bound for the true inter-rater reliability of the assessments.). Test–retest (intra-rater reliability) is performed by inviting 50 children per site to return for repeat assessment with the same rater within 7–10 days. For concurrent validity, to assess the GSED against the Bayley-III, a sample size of n=150 per country produces a two-sided 95% CI 0.15 to 0.44, when the estimate of Pearson’s product-moment correlation is 0.3, with an equal spread of participants tested across age and sex.

10.1136/bmjopen-2022-062562.supp1Supplementary data

In the Netherlands, the GSED SF and PF are administered online. A subset of participants (n=32) are interviewed face-to-face to compare method of administration. To determine test–retest reliability (intra-rater reliability), the primary caregiver completes the SF and PS form online and then a second time 7–10 days later.

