### Data collection

#### Measures

##### GSED

###### GSED SF and LF

The creation of the GSED SF and LF is described elsewhere.^10^ Briefly, we constructed an item bank from previously gathered data and compiled cross-sectional and longitudinal data from 31 countries representing over 73 000 anonymised children with 109 079 assessments (using 22 established ECD instruments).^6 13 14^ Using subject matter expert input and statistical modelling,^15^ we developed two measures intended tocapture child development at population-level and/or to evaluate programmatic impacts: a caregiver-reportedmeasure (GSED SF), and a directly adminsitered measure (GSED LF).^10^ The measures are created paper-based and app-based (GSED App) with built-in administration rules and supporting media-files (see below).

The GSED SF includes 139 items representing emerging skills and behaviours within cognitive, motor, language and social-emotional domains. All items are presented as questions to the caregiver, with binary response options (Yes/No and ‘Don’t Know’) that use start rules based on the child’s age, and stop rules based on age and performance. Assessors record caregiver’s responses, regardless of the assessor’s observations. In the Netherlands only, the GSED SF is completed online by caregivers. The GSED SF administration includes sounds, images and short video clips that assist in understanding, interpretating and administering the items.

The GSED LF includes 155 items capturing similar domains to the SF but, observed by the assessor following start and stop rules based on the child’s age and responses. LF items must either be observed incidentally or by eliciting the behaviour or both, depending on the item. Items are organised into three grids (A, B and C) that enable assessors to measure the child’s performance on similar tasks in succession, making the administration easier for both assessors and children. To further facilitate administration, icons are placed next to each item that inform the assessor whether the item is observed, demonstrated to or by the child, listened for or spoken to the child. The GSED LF uses a locally constructed and low cost kit with basic materials that the child interacts with to demonstrate abilities. The kit is created by local teams with detailed guidance from WHO. Responses of all LF items are binary (skill observed/not observed).

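### Alternating the order in the adaptive-versus-fixed comparison balances visit effects but not unequal carry-over; report the mode difference by order, with a first-administration comparison beside it

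*Protocol article*

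**What the plan says.** Box 2 in the Adaptive testing section sets out the comparison: "Both the adaptive test and the fixed test are administered with the same subsample during two separate visits alternating the order of administration". It takes place "in the subsample designated for predictive validity analyses (n=502 per site) in three sites". The D-score distributions under the two modes are compared by a z-test of their equivalence and by plots of concordance, and the score difference is related to background variables.

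On test length, the same section cites earlier simulations in which "theoretically substantial gains in the precision of scores are possible when using adaptive testing even if administering fewer items". Its stopping rule is: "Once the programme establishes a reliable score, the administration is terminated". The fixed forms are described under GSED SF and LF: "The GSED SF includes 139 items representing emerging skills and behaviours within cognitive, motor, language and social-emotional domains". Those items "use start rules based on the child’s age, and stop rules based on age and performance", and the 155-item LF has start and stop rules too. The article does not say how many items one child meets under either mode.

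Sampling frame and schemes describes the host subsample: "504 children per site are randomly selected for re-evaluation 6 months later to assess predictive validity (primary aim". The same section allocates children to the sampling schemes by a randomisation procedure within sex and age groups. The article calls adaptive testing a secondary, exploratory aim.

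**The concern.** Each child is tested twice, and the second score may be affected by the first session: the child has practised a task, or the caregiver has been prompted to watch for a skill. If that effect is the same whichever mode comes first, alternating the order removes it. If it depends on which mode came first, alternation leaves part of it in the mean difference.

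The two modes differ in how much they expose. The adaptive test is intended to be shorter and stops once the score is reliable enough. A child who takes the fixed form first may therefore have met more of the items that the adaptive test later picks than a child tested in the reverse order. That would tend to raise the adaptive score, which could create a difference between modes or hide a real one. Recruiting more children narrows the interval around the shifted value and does not move it back.

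**Working it through.** **Inputs from the article.** Two modes, two visits, alternating order; 502 children per site at three sites (Box 2), so 3 × 502 = 1506 children and, with equal orders, 753 per order. Sampling frame and schemes gives 504 for the same subsample. The two figures should be reconciled, but the gap does not affect what follows. The article gives no margin, SD or power for this comparison, so there is no stated figure to reproduce.

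**Assumed inputs.** Scores in between-child SD units at a given age; within-child correlation 0.8 (range 0.5 to 0.92); carry-over difference 0 to 0.20 SD. Where D-score units are shown, the SD is taken as 5, the prior SD given under Statistical analysis.

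**1. What the mean difference estimates.** Let τ be the true adaptive-minus-fixed difference, π the second-visit effect, λF the carry-over from a fixed session into a later adaptive score, and λA the carry-over from an adaptive session into a later fixed score.

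- Adaptive first: mean difference = τ − π − λA
- Fixed first: mean difference = τ + π + λF
- Average over equal orders = τ + (λF − λA)/2

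The visit effect π cancels; half the carry-over difference stays. A simulation with 1506 children and 4000 runs agrees. Equal carry-over gave a bias of 0.000; λF = 0.5 and λA = 0.25 D gave 0.126 (formula 0.125); λF = 1 and λA = 0.5 D gave 0.251 (formula 0.25).

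**2. Precision of the paired comparison.** SD of the within-child difference = √(2 × (1 − 0.8)) = 0.632. SE = 0.632/√1506 = 0.0163 SD.

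**3. Size over a range of assumed carry-over differences.**

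| λF − λA (SD) | Bias (SD) | Bias/SE |
|---|---|---|
| 0 | 0 | 0 |
| 0.02 | 0.01 | 0.6 |
| 0.05 | 0.025 | 1.5 |
| 0.10 | 0.05 | 3.1 |
| 0.15 | 0.075 | 4.6 |
| 0.20 | 0.10 | 6.1 |

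Negative carry-over differences give the mirror image. For the 0.15 row, a correlation of 0.5 (SE 1.0/√1506 = 0.0258) gives a ratio of 2.9, and 0.92 (SE 0.4/√1506 = 0.0103) gives 7.3. In D-score units the bias in that row is 0.075 × 5 = 0.375.

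**4. Can the paired data reveal the problem?** Only weakly. An order term in the paired model isolates π + (λF + λA)/2, which says nothing about λF − λA. The usual test compares the sum of each child's two scores between orders. With SD 5 and 753 per order, its detectable λF − λA at 80% power is 1.25 to 1.41 D for correlations of 0.5 to 0.92, that is 0.25 to 0.28 SD. Every row of the table lies below that.

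**5. First administrations only.** Adaptive-first children at visit 1 against fixed-first children at visit 1 estimates τ with no carry-over. SE = √(2/753) = 0.0515 SD; 95% half-width = 1.96 × 0.0515 = 0.10 SD, or about 0.51 D.

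**The case against.** The strongest reply is that unequal carry-over is conjecture. The article has no carry-over data and gives no interval between the two visits. The adaptive test also concentrates on items near the child's level, where prior exposure could matter most, so a shorter session need not leave less carry-over. This stands: size, sign and even existence are unknown, and the ratios in the table show what an assumed bias would do, not that one is present. The algebra also stands: alternation alone gives no protection against it.

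Three stronger readings are tempting and are not supported.

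- **That the fixed form exposes far more items.** The article supports only fewer items under adaptive testing. The fixed forms have start and stop rules, so a child does not meet all 139 or 155 items.
- **That half of the fixed scores in the predictive cohort are second exposures.** With equal orders that is so only at three sites, on the one occasion when both modes are given. Over seven sites it is 753/(7 × 504) = 753/3528 = 21% on that occasion, and about 11% counting baseline and 6 months together. The article does not say that second-visit fixed scores enter the predictive analysis.
- **That the primary analyses are materially harmed.** Suppose the carry-over into fixed scores is as large as 0.10 SD. A shift in half the records adds 0.25 × 0.10² = 0.0025 to a variance of 1, which lowers the correlation at those sites by about 0.1%. For site DIF, if the crossover is at baseline, about 251/1248 = 20% of records shift: 0.20 × 0.10 × 5 = 0.10 D. The Sample size section implies (88.86 − 1.1)/21.6 = 4.06 D per logit, so this is about 0.025 logit against a target of 1 logit. A uniform shift in ability is not DIF in any case.

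It is also fair to say that order terms may stand in a full protocol or analysis plan that is not shown. Their absence from an article is not the complaint. The point concerns what the stated design can and cannot balance.

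**Conclusion.** The point holds in a limited form. As described, the crossover balances visit effects and equal carry-over, and leaves half of any carry-over difference in the mean adaptive-minus-fixed score. With 1506 children and a correlation of 0.8, a carry-over difference of about 0.06 SD would already produce a bias of two standard errors (2 × 2 × 0.0163 = 0.065). Whether a difference of that size exists cannot be settled from the article. The bias formula rests on roughly equal numbers in the two orders and additive effects; the sizes rest on the assumed correlation and carry-over.

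This is a minor improvement to an exploratory comparison that also uses concordance plots. It is not a threat to predictive validity, calibration or the site DIF analysis.

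**What to change.** Keep the paired design and add three things.

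1. Allocate the order of the two modes with the randomisation procedure already used for the sampling schemes, within age and sex groups. Alternation does not rule out random allocation, so this may only need stating. It is what makes the two groups comparable at the first visit.
2. Include order in the paired analysis and report the mode difference separately for each order.
3. Report the first-administration comparison beside the paired estimate as a sensitivity analysis. Do not use a carry-over test to choose between them, since its power is low.

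No extra children or visits are needed. The cost is a few lines of analysis wording and an order variable for each child; the article does not say whether the app stores one. The first-administration interval, ±0.10 SD, is about three times as wide as the paired one (1.96 × 0.0163 = ±0.03 SD), and as wide as the largest bias in the table. It is therefore a check reported alongside and does not replace the paired result.

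Second-exposure fixed records should not be set aside from the primary analyses. Doing so would cut a site from 1248 to about 997 (1248 − 251), below the number that the Sample size section requires, to avoid an effect shown above to be negligible. The figures 502 and 504 for the same subsample should be made to agree.

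### Order of adaptive and fixed testing is set by alternation, with no order term stated for the analysis of the D-score difference; a random order and an order term would be a nearly free improvement

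*Protocol article*

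**What the plan says.** Box 2 of the Protocol article (Adaptive testing) describes a two-period, within-child comparison: the two modes are "administered with the same subsample during two separate visits alternating the order of administration to investigate the difference between the two modes of administration". The work is done "in the subsample designated for predictive validity analyses (n=502 per site) in three sites".

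Two analyses of the mode difference are named. One compares the D-score distributions, "using a z-test to assess the equivalence of the two modalities and plotting the results to show the level of concordance". The other is the "relation of the difference between the two D-scores to background variables". Neither is said to include a term for order or period.

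The study does have a random mechanism elsewhere. Under Sampling frame and schemes, "children are allocated by sex and age groups using a randomization procedure to one of several sampling schema", and the predictive-validity subsample is itself chosen at random. That text does not extend randomisation to the order of the two modes. Box 2 does not say whether order alternates by child, assessor, day or stratum, who sets it, or who books the visits.

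**The concern.** Alternation is a deterministic rule. If it runs child by child, anyone who schedules visits and knows the last order also knows the next one, and could fit particular children to particular slots without meaning to.

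This matters because of what the difference contains. Some time passes between the visits, and children in this age range develop quickly. The score used is the D-score, not the age-standardised DAZ, so growth stays in the difference, together with any familiarity from the first visit. A child tested adaptively second has that gain added to adaptive minus fixed; a child tested adaptively first has it subtracted. If children with some characteristic were over-represented in one order, the background-variable analysis would suggest that the adaptive form behaves differently for them when it does not. That analysis bears on whether adaptive testing can be trusted across subgroups.

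**Working it through.** The plan gives no figure for this point, so there is none to reproduce. The check derives the bias and puts a range on it.

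**Model.** For each child, D = adaptive − fixed = τ + π·s + error. Here τ is the true mode difference, π is the gain from first to second visit, and s = +1 if adaptive comes second and −1 if it comes first. Let p1 and p0 be the shares with adaptive second in the two halves of a binary background variable that has no true relation to D.

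- Spurious difference between the halves = 2π(p1 − p0).
- Bias in the mean mode difference = π(2p − 1), with p the overall share. This is zero at 50:50, which alternation approximately delivers.

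**Inputs from the document.** The item difficulties span 1.1 to 88.86 D-score points (Sample size). The substudy has 502 children per site in three sites, 3 × 502 = 1506 (Box 2). The sampling section gives 504 for the same subsample, which would make 1512. The two counts should be reconciled, but the gap does not affect this point.

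**Assumed inputs.** The document states neither the gain nor the interval between visits. Spreading the item span evenly over 36 months gives (88.86 − 1.1)/36 = 2.44 points per month, or about 0.56 per week. With visits one to two weeks apart, π is 0.56 to 1.12. This is only a rough scale: an item range is not a child's trajectory, and the sampling section says development is faster in the youngest. The 60/40 versus 40/60 split, p1 − p0 = 0.20, is also an assumption.

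**Result.** 2 × 0.56 × 0.20 = 0.22 points; 2 × 1.12 × 0.20 = 0.45 points.

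Over a wider grid of assumptions, the spurious difference in D-score points is:

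| Gain π | p1 − p0 = 0.05 | 0.10 | 0.20 | 0.30 |
|---|---|---|---|---|
| 0 | 0 | 0 | 0 | 0 |
| 0.5 | 0.05 | 0.10 | 0.20 | 0.30 |
| 1 | 0.10 | 0.20 | 0.40 | 0.60 |
| 2 | 0.20 | 0.40 | 0.80 | 1.20 |

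**Scale.** With an assumed SD of 4 points for the within-child difference, the standard error of the contrast between halves is about 2 × 4/√1506 = 0.21. The 0.22 to 0.45 range is therefore roughly one to two standard errors.

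**Alternation that nobody steers.** In simulation with 1506 children, p1 − p0 averages about 0 under both unsteered alternation and simple randomisation, with an SD of about 0.026 for each. Predictability is the weakness; balance as such is not.

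**Effect of an order term.** In 2000 simulated datasets (N = 1506, π = 1, p1 − p0 = 0.20, SD 4), the mean spurious slope was 0.40 without an order term and 0.00 with one. The spread of the estimate was about 0.21 in both cases.

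**The case against.** The case against is strong on several counts.

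- **The wording may mean no more than counterbalancing.** The Schedule section uses that idea for the comparison with Bayley-III or Griffiths. A reader might infer that unblinded assessors can foresee every next assignment. Whoever administers the adaptive test must know its mode, but the document does not say how the sequence runs or who books visits, so foresight is conditional on child-by-child alternation known to the scheduler.
- **Stratification is not ruled out.** A reader might infer that order ignores age and sex. The text is silent, and alternating within those groups is compatible with it.
- **Foreknowledge has less to act on than in a parallel-group trial.** The subsample is chosen at random and every child gets both modes. No motive for consistent steering is apparent. A 60/40 versus 40/60 split would mean about 0.10 × 753 = 75 children displaced in each half, all in the same direction.
- **A between-child comparison at the first visit is not planned.** Any bias there would concern an analysis that Box 2 does not name.
- **Order is observed**, so it can be adjusted for, and model detail may sit in an analysis plan that is not shown. The aim is explicitly exploratory.

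All of this limits severity. What stands is that the article states an assignment rule and does not simply leave it open. The rule is weaker than the random procedure the study already uses, and a named analysis is the one exposed to it.

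**Conclusion.** The point holds as a minor one. The stated rule is alternation, and the analysis of the D-score difference against background variables is described without an order term. A spurious relation needs two things together: a gain between visits, and a link between order and the background variable. Under the assumptions above its size is about 0.2 to 0.45 D-score points; with either condition absent it is zero. The document shows no such link.

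It would be tempting to conclude that the adaptive-versus-fixed comparison is biased as a whole. The documents do not support that. Each child is their own control, and a near 50:50 split of orders largely cancels the gain from the mean mode difference. No primary aim is touched.

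**What to change.** In Box 2, replace alternation with random 1:1 assignment of order, generated by the existing randomisation procedure or the GSED App, within site and age/sex group, and revealed only after the first visit has been booked. Include order in the paired mode comparison and in the model of the D-score difference on background variables. Add order by age: growth is faster in the youngest, so a single order term may leave some bias if order is linked to age.

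If data have already been collected by alternation, tabulate baseline variables by order, adjust for order and order by age, and state how the alternation was run.

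The cost is a sentence or two, a list loaded into the App, and two terms in an exploratory model. No extra children, visits or staff are needed. Order counts may be slightly unequal within a stratum.

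### Equivalence of adaptive and fixed administration is assessed by a z-test with no margin, and the test is not stated to be paired although every child takes both modes

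*Protocol article*

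**What the plan says.** The Adaptive testing section (Box 2) of the protocol article sets out the comparison of the two modes.

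- **Design:** "Both the adaptive test and the fixed test are administered with the same subsample during two separate visits alternating the order of administration". Each child therefore contributes one score per mode, with order alternated.
- **Target:** "the comparison of the D-score distribution under the adaptive testing procedure with the D-score distribution under the fixed GSED administration".
- **Method:** "using a z-test to assess the equivalence of the two modalities and plotting the results to show the level of concordance".
- **Further analysis:** "relation of the difference between the two D-scores to background variables".
- **Size:** the work is done "in the subsample designated for predictive validity analyses (n=502 per site) in three sites". The section Sampling frame and schemes gives the same subsample as "504 children per site are randomly selected for re-evaluation 6 months later to assess predictive validity".

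No margin, significance level, confidence-interval rule or agreement limit is stated for this comparison. The form of the z-test (paired or two-sample, per site or pooled) is not stated either. The article lists developing and validating the adaptive algorithm as a secondary aim and labels all secondary aims exploratory.

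**The concern.** An ordinary z-test takes no difference as its null hypothesis. Rejecting that null shows that the modes differ; failing to reject it shows only that the data did not settle the matter. To claim equivalence, one must rule out differences larger than a stated size, and no size is stated.

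Without a margin, the outcome depends on precision rather than on whether the difference matters, and precision here depends heavily on pairing. D-scores rise steeply with age. A two-sample test on raw D-scores would carry the whole age spread in its error term and could miss a real shift between modes. A paired test removes the age spread and, with about 500 children per site, could reject on a shift of no practical importance.

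A comparison of means also cannot see a difference in spread. The Statistical analysis section says D-scores are EAP estimates with a prior centred on the average for the child's age, and accepts that such estimates understate variability. If one mode carries less information, its scores are pulled harder towards the age mean. Group means could then agree while the spreads differ.

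At stake is whether the study can support a statement that the adaptive form may stand in for the fixed form.

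**Working it through.** The article gives no power, margin or expected difference for this comparison, so there is no stated figure to reproduce. The calculations below illustrate how a z-test would behave.

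**Inputs from the article**
- n = 502 per site (Box 2) or 504 (Sampling frame and schemes); three sites give 1506 or 1512.
- SD of 5 D-score units. This is the SD of the age-conditional EAP prior in Statistical analysis, used here as a stand-in for the within-age SD.
- Item difficulties from 1.1 to 88.86 D-score units (Sample size).

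**Assumptions**
- All-age SD of raw D-scores 15 to 20. The item range makes this plausible but does not fix it.
- Subsample ages up to 41 months, consistent with the footnote to Table 2 on the ECDI subsample.
- Within-age correlation between modes r = 0.8.
- Two-sided 5% level. The article states this only for the DIF sizing.

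**1. Unpaired z-test on raw D-scores.** The largest non-significant observed difference is 1.96 × SD × √(2/n).

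| n | SD 15 | SD 20 |
|---|---|---|
| 504 (one site) | 1.85 | 2.47 |
| 1512 (three sites) | 1.07 | 1.43 |

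Using 502 and 1506 gives 1.86 and 2.47, and 1.07 and 1.43, so the mismatch in n has no effect. Divided by 5, the table values are 0.37 to 0.49 of the prior SD per site and 0.21 to 0.29 pooled.

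**2. Paired z-test.** In units of the within-age SD, SE = √(2(1 − 0.8)/504) = 0.028. The significance threshold is 1.96 × 0.028 = 0.055, so an observed difference of 0.06 SD (0.3 units if the SD is 5) is significant at a single site.

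**3. Size of the gap.** The paired SE is 5 × 0.028 = 0.14 units. The unpaired SE is 15 × √(2/504) = 0.94 to 20 × √(2/504) = 1.26 units, about 7 to 9 times larger.

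**4. A true shift of 1 unit, pooled n = 1506.** The mean difference has a true SE of √(2 × 25 × 0.2/1506) = 0.081. With SD 15, the unpaired test needs an observed difference above 1.07. The chance of missing the shift is Φ((1.071 − 1)/0.0815) = Φ(0.88), about 81%. With SD 20 it is close to 100%. The paired test would almost never miss it, since 1/0.081 is about 12 standard errors.

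**5. What an equivalence test could show.** With two one-sided 5% tests, paired, and a true difference of zero, the smallest margin with 90% power is (1.645 + 1.645) × SE. For SD 5 and r = 0.8 this is 0.46 units per site (n = 502) and 0.27 pooled (n = 1506). For illustration only, a margin of 0.15 SD gives 0.15/0.028 = 5.3 standard errors per site, and power above 99%. Under these assumptions the planned sample is ample for a proper equivalence analysis.

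**The case against.** The strongest reply is that Box 2 condenses a fuller protocol and may describe the test loosely. A z-based pair of one-sided tests is not excluded. Pairing, order adjustment and agreement limits are commonly settled in an analysis plan. The z-test is also supplemented by a concordance plot and by an analysis of how the difference between scores relates to background variables. The aim is exploratory, and no primary objective depends on it.

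Much of this stands, and it rules out three stronger readings that a reader might infer.

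- **That a non-significant result will be taken as equivalence.** The article writes no decision rule for this comparison. The Reference scores section does check an assumption of equal distributions by significance tests on site effects, which makes the inference natural, but it concerns a different analysis.
- **That the pairing is ignored.** The form of the z-test is simply unstated. Comparing two distributions hints at a two-sample test, but the next clause analyses the difference between the two scores.
- **That this test alone decides whether the adaptive form is valid.** The plot and the background-variable analysis also contribute.

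The magnitudes also depend on assumed values, and the article commits to neither the paired nor the unpaired test. They show what could happen under each reading and do not measure an error already made.

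One thing is not answered. The article does more than leave a detail open: it names a test and assigns it the task of assessing equivalence. Any z-based equivalence procedure needs a margin, and none is given.

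**Conclusion.** The point holds in a limited form: the z-test as described, with no margin, cannot establish equivalence, and the article does not say that it is paired.

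The possible consequence runs in both directions. If unpaired on raw D-scores, differences up to about 1.9 to 2.5 units per site, or 1.1 to 1.4 units pooled, could pass as non-significant; this rests on an assumed all-age SD of 15 to 20. If paired, a difference of about 0.06 SD per site could be significant; this rests on r = 0.8. Any conversion between units and SD also treats the prior SD of 5 as a within-age SD.

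Severity is moderate. The aim is secondary and exploratory, and the planned data would support the right analysis. The 502 versus 504 discrepancy is real but editorial and changes none of these results.

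**What to change.** 1. Replace the z-test by a paired analysis of within-child differences between modes, on DAZ or D-score.
2. State an equivalence margin in advance and justify it on substantive grounds. Judge the confidence interval for the mean difference, or two one-sided tests, against it. The sponsor must supply the margin; the article offers no basis for a particular value.
3. Account for order of administration in the model, and say whether the conclusion is drawn per site or pooled over the three sites.
4. Quantify the planned concordance plot with limits of agreement and the ratio of the two SDs, so that a difference in spread is visible as well as a shift in means.
5. Reconcile n = 502 in Box 2 with n = 504 in Sampling frame and schemes.

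The cost is analysis wording only. The paired, order-alternated data are already planned, and no extra children or visits are needed. The one real demand is that a margin must be chosen and defended.
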